### Study outcomes

Primary endpoints include graft loss and patient mortality. Graft loss is defined as requiring maintenance dialysis for more than 3 months or re-transplantation. The cause of graft loss will be pursued. Patient mortality will be classified into cardiac, noncardiac, and unknown death. Subjects who drop out from the study will be traced for this information with the help of National Health Insurance Cooperation and Korea Statistical Information Service.

Secondary endpoints include renal functional deterioration, acute rejection, cardiovascular event, albuminuria, new-onset diabetes after transplant, and QoL. Renal functional deterioration is defined as a decrease in eGFR to less than 30 mL/min/1.73 m^2^ after transplantation. Serum creatinine will be measured by an isotope-dilution mass spectrometry (IDMS)-traceable method. Estimations for defining renal deterioration will be based on both the four-variable Modification of Diet in Renal Disease formula [13], and Chronic Kidney Disease Epidemiology Collaboration creatinine equation [14]. Cardiovascular events include myocardial infarction, coronary revascularization, stroke and new onset or aggravation of congestive heart failure.

Data on other adverse outcomes including episodes of infection, malignancy, recurrence of original renal disease, fracture, chronic liver disease, and hospitalization will also be collected.

### Reference populations for the evaluation of chronic complications

To compare the risk of developing chronic medical complications, we plan to use two reference populations. One consists of approximately 3,000 CKD patients who are enrolled in the KoreaN cohort study for Outcome in patients With Chronic Kidney Disease (KNOW-CKD), and the other is the general Korean population compiled from the compulsory national health insurance program without any claims under the diagnosis of CKD. Data from the KNOW-CKD will be used for a pooled analysis to provide the incidence rate ratios adjusting for various risk factors. For the comparison between the general population and the KNOW-KT, standardized incidence rates will be presented.

### Biospecimen banking

As baseline DNA samples, 4 mL of the whole blood from recipients, collected in ethylenediaminetetraacetic acid tube will be used. Another 10 mL of whole blood will be collected in serum separation tube and centrifuged within 1 hour for serum sample stock. Ten mL of morning first-voided urine samples will be taken for urine sample stock and urine sediments will also be prepared by centrifugation. Aliquots of the serum and urine samples will be stored in a deep freezer (−70 °C). Serum and urine samples will be collected at baseline and year 1, 3, and 5 after enrollment. For RNA extraction and storing, 10 mL of whole blood will be collected in PAXgene® tubes (Qiagen Inc., Valencia, CA, USA) at year 1, 3, and 5 visits. DNA samples from donors will be collected in the same manner as in the recipients. Sampling, delivery, and storage of samples will be under strict monitoring throughout the study period.

### Ethical considerations

The study is conducted under the Declaration of Helsinki. The regional ethical committee and Institutional Review Board of each participating center approved the study protocol. Informed consent in written form is essential to recruit study population, for both donor and recipients. It was also registered in an international clinical trial registry (NCT02042963 at http://www.clinicaltrials.gov) on January 20^th^, 2014.

### Statistical considerations

Descriptive analysis will be performed for baseline data. Normally distributed continuous variables will be presented as mean ± standard deviation. For nonparametric continuous variables, median with interquartile ranges will be used as the summarizing values. Categorical data will be presented with numbers and proportions. Comparison of continuous variables will be conducted with t-test or Wilcoxon rank-sum test, and categorical variables will be compared using chi-squared test or Fisher’s exact test as appropriate.

Survival time of grafts or patients, time to cardiovascular outcomes (myocardial infarction, ischemic stroke, etc.) and renal outcomes (graft loss, renal functional deterioration, acute rejection, etc.) will be estimated using Kaplan-Meier curves. Cox proportional hazard models will be used for comparison for the incidence of those outcomes among groups with and without each risk factor. However, patient death is a competing cause of renal outcomes or cardiovascular outcomes. Therefore, we will adopt competing risk models in evaluating the contributions of risk factors for those outcomes. For time-varying covariates that break the proportional hazard assumption, an extended Cox model to compare the risk of outcomes will be used.

Since more than 60% of KT patients have CKD at 1 year after transplantation [4], and CKD patients often have a non-linear eGFR decline or a prolonged period of non-progression [15], the pattern of renal functional deterioration will be explored using the Bayesian smoothing technique [16]. We will compare eGFR decline in serial measurements using a mixed linear model considering the longitudinal nature of our data. The generalized estimating equation will be used for estimating the slope of the eGFR in the area of steady and linear eGFR decline.

We will enroll 1,000 KT patients from participating centers. We assumed that the incidence of cardiovascular complications at 5 years would be 22% [17]. With that assumption, the sample size will detect a relative risk of 1.46 or more by a risk factor with a prevalence of 50% at 5% alpha and 20% beta in an analysis using Cox regression model. Assuming the same significance level and statistical power, for a risk factor with prevalence of 12%, the sample size would detect a relative risk of 2.00 or higher as significant from same statistical model. Analysis will be performed by using SAS 9.3 (SAS Institute, Cary, NC, USA). Statistical analysis will be 2-sided, and p-value < 0.05 will be considered statistically significant.

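### Kaplan-Meier is the only named estimator for graft, renal and cardiovascular outcomes that the plan says compete with death; read as absolute risk, its complement overstates cumulative incidence

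*Protocol article*

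**What the plan says.** All the analysis text is in the protocol article, Statistical considerations.

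- **Estimator.** One sentence covers every time-to-event outcome. It opens with "Survival time of grafts or patients, time to cardiovascular outcomes (myocardial infarction, ischemic stroke, etc" and ends with "renal outcomes (graft loss, renal functional deterioration, acute rejection, etc.) will be estimated using Kaplan-Meier curves".
- **Competing event.** After assigning risk-factor comparisons to Cox models, the section says "However, patient death is a competing cause of renal outcomes or cardiovascular outcomes".
- **Remedy.** It concludes that "we will adopt competing risk models in evaluating the contributions of risk factors for those outcomes". No cumulative incidence function is named for the curves or incidences.

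Two other places decide what happens to deaths in those curves. Study outcomes says "Graft loss is defined as requiring maintenance dialysis for more than 3 months or re-transplantation", so death is not graft loss. Study design and study population ends follow-up at 9 years or earlier at death, graft failure or drop-out.

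**The concern.** The article states a premise (death competes) and acts on it for only half of the analysis. The risk-factor models allow for competing death, while the absolute risks stay with an estimator that treats a death as if the patient could still have had the event later.

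Absolute risk is a main product of this cohort. The Abstract promises allograft survival and cardiovascular event results and a description of the natural course. The Discussion looks ahead to comparison with Western cohorts. Follow-up runs to 9 years, and the gap between one minus Kaplan-Meier and cumulative incidence widens with time. If two cohorts differ in mortality, a comparison of their Kaplan-Meier complements mixes that difference with the difference in event risk.

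**Working it through.** **The plan's own figure.** The detectable relative risk of 1.46 (50% prevalence, two-sided 5% alpha, 80% power) reproduces. Schoenfeld's formula gives (1.960 + 0.842)² / (0.25 × (ln 1.46)²) = 219.2, so 220 events, and 220 / 0.22 = 1,000 patients. This figure does not depend on the present point.

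**Inputs**
- Cardiovascular incidence of 22% at 5 years: Statistical considerations. That this is a Kaplan-Meier risk is an assumption.
- Horizon of 9 years: Study design and study population.
- Graft loss hazard of 2% per year: assumed, because the article gives none.
- Death hazard of 0.5%, 1%, 2% or 3% per year: assumed, because the article gives no mortality figure.

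**Formulas** (constant cause-specific hazards; λ for the event, μ for death)
- Kaplan-Meier complement with deaths censored: 1 − exp(−λT)
- Cumulative incidence: λ/(λ+μ) × [1 − exp(−(λ+μ)T)]

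For any μ above zero the first exceeds the second, so the direction does not depend on the assumed values.

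**Graft loss, λ = 0.02, T = 9.** Kaplan-Meier: 1 − exp(−0.18) = 16.5%. Cumulative incidence at μ = 0.005: 0.02/0.025 × [1 − exp(−0.225)] = 0.8 × 0.2015 = 16.1%. At μ = 0.03: 0.4 × [1 − exp(−0.45)] = 0.4 × 0.3624 = 14.5%.

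**Cardiovascular events, T = 9.** λ = −ln(0.78)/5 = 0.0497. Kaplan-Meier: 1 − exp(−0.0497 × 9) = 36.1%. Cumulative incidence at μ = 0.005: 0.9086 × 0.3887 = 35.3%. At μ = 0.03: 0.6236 × 0.5119 = 31.9%.

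| Death per year (assumed) | Graft loss at 9 years: KM vs cumulative incidence | Relative excess | Cardiovascular at 9 years: KM vs cumulative incidence | Relative excess |
|---|---|---|---|---|
| 0.5% | 16.5% vs 16.1% | 2% | 36.1% vs 35.3% | 2% |
| 1% | 16.5% vs 15.8% | 4% | 36.1% vs 34.6% | 4% |
| 2% | 16.5% vs 15.1% | 9% | 36.1% vs 33.2% | 9% |
| 3% | 16.5% vs 14.5% | 14% | 36.1% vs 31.9% | 13% |

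**At 5 years** the cardiovascular gap is smaller: 22.0% against 21.7%, 21.5%, 21.0% and 20.5% down the same four rows, or about 1-7% relative.

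**Sensitivity to reading the 22%.** If 22% is already a cumulative incidence, solving the second formula for λ at 5 years gives λ = 0.0504 (μ = 0.005) and 0.0539 (μ = 0.03). The 9-year figures become 36.4% against 35.7%, and 38.4% against 34.0%. The relative excess is again about 2-13%.

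**The case against.** The case for leaving the text alone has several parts.

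- **The primary objective is protected.** That objective is to delineate predictors, and the risk-factor models will use competing risk methods. This stands, and it confines the point to the descriptive curves and incidences.
- **The article does not say that one minus Kaplan-Meier will be reported as cumulative incidence.** This is true. A graft curve labelled as death-censored is a legitimate quantity, and graft survival with death counted as failure is properly estimated by Kaplan-Meier. But no other estimator of absolute risk is named, and the graft loss definition leaves death out, so a reader of the curves has nothing else to use.
- **Mortality may be low.** The Background describes Korean graft and patient survival as very good. At 0.5-1% death per year the 9-year excess is only about 2-4% relative. This stands, which is why the size is given as a range.

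A reader might also infer more than the documents support:

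- **That the reference-population comparisons are biased.** They are not. The section on reference populations uses adjusted incidence rate ratios against the CKD cohort and standardized incidence rates against the general population. Neither uses Kaplan-Meier.
- **That subgroup curves, for example in older or diabetic recipients, are distorted by a known amount.** The article gives no mortality by subgroup, so this cannot be calculated.
- **That a new group test is needed.** Group comparisons already go to Cox and competing risk models, so a test such as Gray's would replace nothing.
- **That leaving cardiac death out of the cardiovascular endpoint is an error of the same kind.** The definition reads "Cardiovascular events include myocardial infarction, coronary revascularization, stroke and new onset or aggravation of congestive heart failure", and separately "Patient mortality will be classified into cardiac, noncardiac, and unknown death". This is a choice of endpoint that contradicts nothing. Cardiac deaths are captured under the primary mortality endpoint. Moving them into the cardiovascular composite would also leave the unknown class unassigned.

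**Conclusion.** The point holds for the descriptive estimates of graft loss, renal functional deterioration, acute rejection and cardiovascular events. The article fixes Kaplan-Meier for them while saying that death competes with them. Read as absolute risk, the complement of those curves is too high whenever anyone dies before the event.

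The direction is certain; the size is not. With death at an assumed 0.5-3% per year and constant hazards, the 9-year excess is about 0.4 to 2.0 percentage points for graft loss (at an assumed 2% per year) and about 0.7 to 4.1 points for cardiovascular events. The low end is negligible. The high end would matter when absolute risks are set beside those of other cohorts. The risk-factor results, the reference-population rates and the sample size statement are untouched.

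**What to change.** In Statistical considerations:

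1. Keep Kaplan-Meier for patient survival and for the composite of graft loss or death.
2. For graft loss, eGFR below 30, acute rejection and cardiovascular events, report Aalen-Johansen cumulative incidence with death as a competing event.
3. Treat graft failure as a further competing event for outcomes whose follow-up it ends. The study design stops follow-up there, but the analysis text names only death.
4. Label any Kaplan-Meier graft curve as death-censored.

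The cost is a few sentences and minor extra code. Dates of death and graft loss are needed for the primary endpoints anyway, so no new data or patients are required. Reported incidences will be slightly lower than their Kaplan-Meier counterparts.

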
Complication events will be collected annually as an event-based report including the date in which complication occurred. Follow-up examinations are scheduled once a year. Evaluation schedule of the KNOW-KT at each visit (Table 2) summarized details regarding the schedules for study visits, tests, and questionnaires. Immunosuppressive medications at discharge will be recorded as a baseline, and then they will be recorded annually. Medication adherence will be monitored annually using Health Questionnaires.

**Table 2 T2:** Evaluation schedule of the KNOW-KT at each visit

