## Discussion

Although modern immunologic assessments and potent immunosuppression markedly decreased the acute rejection rate in KT, it fails to suppress chronic rejection due to immunologic and non-immunologic factors; this has becomes a major obstacle for long-term graft survival. Furthermore, as both graft and patient survival improve, KT patients, who are often in the early stages of CKD, become exposed to chronic immunosuppression. Therefore, KT patients can develop many medical complications such as cardiovascular events, metabolic complications, infection, malignancy, and mineral bone disorders as well as chronic rejection. Indeed, chronic medical complications have become a major cause of morbidity and mortality in KT patients.

Antibody-mediated injury is an important cause of immunologic injury in chronic rejection or chronic allograft nephropathy. Because noncompliance is one of main causes of antibody formation, compliance monitoring together with antibody monitoring is included in our prospective study. Hypertension, hyperlipidemia, and diabetes, so called non-immunologic risk factors for chronic allograft nephropathy, are common after KT and are reported to induce chronic damage to allografts.

The nonimmunologic risk factors for chronic allograft nephropathy are among traditional risk factors for cardiovascular disease. Cardiovascular events have been reported to be the most common cause of death in KT patients in Western countries. However, many studies show that racial/ethnic disparities exist in mortality and cardiovascular outcome among CKD patients [18-21]. Transplant outcomes seem to differ according to racial differences [22,23]. Asian KT patients generally have better renal allograft survival and a lower burden of cardiovascular disease than other racial groups. The KNOW-KT, the first large-scale cohort study in Asian KT patients, aims to explore allograft survival rate, cardiovascular events, and metabolic profiles and to investigate the risk factors in Asian or Korean KT patients.

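### The extended Cox model is triggered by a proportional-hazards violation, not by whether the covariate changes after transplantation, so immortal-time bias is left possible for post-transplant exposures

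*Protocol article*

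**What the plan says.** Under Statistical considerations, the protocol article sets the default for risk-factor analyses: "Cox proportional hazard models will be used for comparison for the incidence of those outcomes among groups with and without each risk factor". Because death competes with renal and cardiovascular outcomes, it adds that "we will adopt competing risk models in evaluating the contributions of risk factors for those outcomes". It then gives the rule at issue: "For time-varying covariates that break the proportional hazard assumption, an extended Cox model to compare the risk of outcomes will be used". It does not say at what time a recipient is classified as having a risk factor.

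Much of what the cohort records arises after transplantation:
- Medication: "Immunosuppressive medications at discharge will be recorded as a baseline, and then they will be recorded annually".
- Adherence: "Medication adherence will be monitored annually using Health Questionnaires".
- Complications: "Complication events will be collected annually as an event-based report including the date in which complication occurred".
- Panel reactive antibody: baseline, year 1 and year 5 (Table 2).

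The Discussion explains that non-adherence is a main cause of antibody formation and that for this reason "compliance monitoring together with antibody monitoring is included in our prospective study". Under Study objectives, finding predictors of graft failure, death, and cardiovascular and metabolic complications is the primary objective.

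**The concern.** Two questions need separate answers. The first is whether the covariate's value is known at time zero. If it is not, it must be time-updated, or the clock must start at a landmark, whether or not hazards are proportional. The second is whether the covariate's effect is constant over follow-up. If it is not, the model needs a time-varying coefficient, even for a covariate fixed at baseline.

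The rule joins the two and takes its trigger from the second. A post-transplant exposure that passes a proportional-hazards check is then given no special handling and falls back to the default group comparison. If an analyst forms those groups by whether the factor ever appeared, every recipient in the exposed group had to remain event-free until it appeared. That waiting time is credited to the exposed group and pulls the hazard ratio down, so a harmful factor can look neutral or protective. The direction of findings for the primary objective is at stake.

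**Working it through.** **1. The plan's own figure.** Inputs from Statistical considerations: N = 1,000, 22% cardiovascular events at 5 years (220 events), prevalence p = 0.50, two-sided alpha 0.05, power 0.80. Schoenfeld's formula is events = (1.960 + 0.842)² / [p(1 − p)(ln HR)²].
- HR 1.46, p = 0.50: 7.849 / (0.25 × 0.1432) = 219.2, so 220 events, and 220 / 0.22 = 1,000 recipients. The minimum detectable HR at 220 events is 1.459. This reproduces.
- HR 2.00, p = 0.12: 155 events needed; at 220 events the power is 91.6% and the minimum detectable HR is 1.79. The stated 2.00 is conservative and does not bear on this point.

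The article gives no figure for the coding of exposures, so the size of the possible bias can only be illustrated.

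**2. Possible readings of the rule.**
- Restrictive clause (as worded): only covariates that are both time-varying and non-proportional are sent to the extended model. Changing exposures that satisfy the assumption have no rule.
- Descriptive clause (time-varying covariates break the assumption by their nature): all of them go to the extended model and the bias does not arise.
- Time-varying taken to mean a time-varying effect: non-proportionality is handled, but changing exposures have no rule.

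Two of the three readings leave the handling of post-transplant exposures open.

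**3. Illustration at the study's own event rate.** 300 simulated cohorts per row, N = 1,000, 9 years of follow-up, constant hazard −ln(0.78) / 5 = 0.0497 per year, no drop-out. Assumed: 12% or 50% eventually exposed, onset uniform over the first 1 or 5 years. Fixed coding means ever exposed before the recipient's own event or censoring, counted from transplantation. Brackets give the share of cohorts with p < 0.05.

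| Exposed | Onset window | True HR | Fixed coding | Time-updated |
|---|---|---|---|---|
| 12% | 1 year | 1.00 | 0.91 (7%) | 0.98 (6%) |
| 50% | 1 year | 1.00 | 0.88 (23%) | 1.00 (4%) |
| 12% | 5 years | 1.00 | 0.66 (57%) | 0.98 (4%) |
| 50% | 5 years | 1.00 | 0.54 (100%) | 0.99 (5%) |
| 12% | 1 year | 1.46 | 1.35 (55%) | 1.47 (72%) |
| 50% | 1 year | 1.46 | 1.26 (63%) | 1.45 (97%) |
| 12% | 5 years | 1.46 | 0.95 (4%) | 1.44 (58%) |
| 50% | 5 years | 1.46 | 0.78 (67%) | 1.46 (94%) |
| 12% | 1 year | 2.00 | 1.84 (99%) | 2.01 (100%) |
| 50% | 1 year | 2.00 | 1.74 (100%) | 2.01 (100%) |
| 12% | 5 years | 2.00 | 1.27 (37%) | 1.98 (98%) |
| 50% | 5 years | 2.00 | 1.04 (6%) | 2.00 (100%) |

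**4. Other onset patterns, true HR 1.00, fixed coding.** One million simulated subjects, censored at 9 years, assumed outcome rates of 1%, 2% and 5% per year:
- constant onset of 2-10% per year throughout: 0.36-0.48;
- 10% exposed during year 1, then 2% per year: about 0.60;
- 30% exposed, all within year 1: 0.91-0.93.

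The bias depends mainly on how long recipients must wait for the exposure. It depends little on the outcome rate.

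**The case against.** The article never says that the extended model is used only in this case, and nowhere does it define a group by later exposure. A reader might infer that all other post-transplant factors enter as fixed groups and that the planned results are therefore biased. The text does not support that: the simulations show what such coding would do, not that it is planned.

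The descriptive reading in step 2 is also natural, because when a value changes, the hazard ratio between two recipients changes with it.

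The default comparison suits the many factors known at or near time zero: donor characteristics, HLA typing and crossmatch, baseline comorbidity, and immunosuppression at discharge, which the article treats as baseline. None of these carries immortal time. Powering for a single prevalence of 50% or 12% is consistent with such factors. Acute rejection and new-onset diabetes are named as endpoints ("acute rejection, cardiovascular event, albuminuria, new-onset diabetes after transplant, and QoL"), and no section names them as Cox exposures.

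Finally, this is a condensed article, and a full analysis plan may code each exposure correctly.

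All of this stands as a limit on the claim. It does not remove the point, because the fault lies in a rule the article does state and not in a detail it leaves out. Read as worded, the rule has the wrong trigger.

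A reader might also object that a baseline covariate with a non-proportional effect, such as donor type, gets no remedy. That is an omission a full plan may fill, so it is secondary here.

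**Conclusion.** The point holds in limited form. The stated trigger for the extended Cox model is wrong as worded, and it leaves open how post-transplant exposures that satisfy proportional hazards are coded. Immortal-time bias is thereby permitted, not prescribed.

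If ever/never coding were used, a null exposure would show a hazard ratio of about 0.9 with onset confined to year 1, 0.54-0.66 with onset over 5 years, and 0.36-0.48 with onset over 9 years. With onset over 5 years, a true hazard ratio of 1.46, the study's own detectable effect, would appear as 0.78-0.95. The lowest null values are the severe end of the range.

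These sizes rest on assumed onset patterns and exposure frequencies, a constant outcome hazard, and no drop-out or competing death. They do not apply to factors fixed at or near transplantation. The point deserves correction because predictors are the primary objective and because adherence and antibodies are among the factors the article singles out.

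**What to change.** Replace the sentence with wording such as:

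> Risk factors that arise or are updated after transplantation enter as time-dependent covariates, from the recorded event date or from the visit at which they are first recorded, or from a landmark at the year-1 visit, regardless of any proportional-hazards test; cause-specific hazards are used for these factors. Non-proportional effects of baseline covariates are handled separately with a covariate-by-time term.

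Cause-specific hazards are compatible with the competing-risk approach already announced. They also avoid having to assign a covariate value to recipients who have died, which a subdistribution risk set would require. Discharge immunosuppression can stay a baseline factor.

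No new data collection is needed. The costs are:
- counting-process data sets instead of one row per recipient;
- exact onset dates for complications only: medication and adherence values are carried forward between yearly visits, and antibody results from year 1 to year 5 (4 years), so some exposed time is counted as unexposed;
- with a year-1 landmark, loss of first-year events and no information on exposures that start later.

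### The detectable relative risk of 2.00 at 12% prevalence does not follow from the stated assumptions, which give about 1.79

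*Protocol article*

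**What the plan says.** The sample-size paragraph in the protocol article (Methods, Statistical considerations) starts from a fixed cohort size: "We will enroll 1,000 KT patients from participating centers". It then gives the event assumption: "We assumed that the incidence of cardiovascular complications at 5 years would be 22" per cent. From these it states a first detectable effect: "the sample size will detect a relative risk of 1.46 or more by a risk factor with a prevalence of 50" per cent, "at 5% alpha and 20% beta in an analysis using Cox regression model". The same paragraph makes testing two-sided: "Statistical analysis will be 2-sided, and p-value < 0.05 will be considered statistically significant".

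The second detectable effect is tied explicitly to the first. It opens with "Assuming the same significance level and statistical power", states that "for a risk factor with prevalence of 12%, the sample size would detect a relative risk of 2.00 or higher", and closes with "as significant from same statistical model". The paragraph gives no attrition allowance, covariate adjustment or different event rate that would separate the two cases.

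**The concern.** With cohort size, event rate, alpha, power and model all held the same, only the prevalence differs between the two statements. The detectable relative risk at 12% prevalence is then fixed once the figure at 50% is known, and 2.00 looks too large to be the partner of 1.46.

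These two figures are the article's only quantitative statement of what 1,000 patients can show. The primary objective (Methods, Study objectives) is to identify predictors of graft failure, mortality, and cardiovascular and metabolic complications, and many such predictors will be uncommon, so the second figure matters to a reader. If 2.00 is wrong, the stated sensitivity for uncommon factors is understated, and relative risks between about 1.8 and 2.0 appear to lie below the 80% power limit when they do not. If 2.00 is right because fewer events were assumed, then 1.46 is too optimistic.

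**Working it through.** **Inputs**, all from the sample-size paragraph:
- N = 1,000 and 5-year incidence 22%, so D = 1,000 × 0.22 = 220 events (22% read as the whole-cohort incidence)
- two-sided alpha 5%, z = 1.960; power 80%, z = 0.842; sum 2.802
- prevalence p = 0.50 for the first case and 0.12 for the second

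**Formula** (Schoenfeld, Cox model with a binary covariate): RR = exp[ 2.802 / √(D·p·(1−p)) ]

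**Step 1: reproduce the plan's first figure.** p = 0.50: D·p·(1−p) = 220 × 0.25 = 55; √55 = 7.416; 2.802/7.416 = 0.378; RR = 1.459. This matches 1.46, so the formula and inputs agree with the authors' own result.

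**Step 2: apply the same formula to the second case.** p = 0.12: 220 × 0.12 × 0.88 = 23.23; √23.23 = 4.820; 2.802/4.820 = 0.581; RR = 1.788, not 2.00. On the log scale the stated figure is 0.693/0.581 = 1.19 times the computed one, 19% too large.

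**Step 3: what 2.00 would need.**
- Power at RR 2.00, p = 0.12, 220 events: 0.693 × 4.820 − 1.960 = 1.381, which is 91.6% power.
- Events for 80% power at RR 2.00, p = 0.12: 2.802² / (0.1056 × 0.693²) = 154.7, or about 705 patients at 22%.
- With 154.7 events the first figure would be 1.57.
- Prevalence at which 220 events give RR 2.00: 8.1% (at exactly 8%, RR = 2.006).

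**Step 4: a check free of events, alpha and power.** Under this formula the ratio of the two log relative risks depends only on the prevalences: √(0.25/0.1056) = 1.54. The stated pair gives ln 2.00 / ln 1.46 = 0.693/0.378 = 1.83. Rounding of the relative risks allows only 1.81 to 1.86. Any common attrition, covariate adjustment, alpha or power cancels from this ratio and so cannot reconcile the pair. Rounding of the prevalence does not help either: 11.5% gives 1.81 and 12.5% gives 1.77.

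**Step 5: other methods and readings.**

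| Variant | RR at 50% | RR at 12% |
|---|---|---|
| Stated in the article | 1.46 | 2.00 |
| Schoenfeld, as above | 1.46 | 1.79 |
| One-sided 5% | 1.40 | 1.68 |
| Freedman | 1.47 | 1.62 |
| Freedman, protective factor (inverse RR) | 1.47 | 2.19 |
| Wald, variance from the event split | 1.47 | 1.65 |
| Two proportions, RR | 1.40 | 1.57 |
| Two proportions, odds ratio | 1.54 | 1.84 |
| 22% read as unexposed rate | 1.42 | 1.75 |
| 22% read as exposed rate | 1.51 | 2.19 |
| 30% fewer events, or covariate R² about 0.30 | 1.57 | 2.00 |
| 90% power | 1.55 | 1.96 |
| 1% alpha | 1.59 | 2.03 |

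No row gives 1.46 and 2.00 together.

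**Step 6: simulation** (Cox Wald test, exponential times, 3,000 runs per setting): power was 78.8% at RR 1.46 with 50% prevalence, 88.6% at RR 1.79 with 12%, and 96.9% at RR 2.00 with 12%. For a harmful factor at 12% prevalence the true 80% limit is therefore somewhat below 1.79, further still from 2.00.

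**The case against.** The best defence is that the sentence is safe as written. A relative risk of 2.00 or more at 12% prevalence is detected with at least the promised 80% power; only the reading of 2.00 as the 80% limit fails. That is true, and the study is not underpowered on this account. The sentence nevertheless offers 2.00 at the same power as the first figure, and at that power it is not the limit.

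It can also be said that nothing depends on the number. The cohort size is stated first rather than solved from 2.00, no analysis uses a detectable effect to select risk factors, and every factor will be tested at two-sided 5% whichever figure is printed. This stands: the harm is to what readers take the cohort to be capable of, not to the analysis.

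Thirdly, the article condenses a fuller protocol, and an unstated allowance of about 30% fewer events would give 2.00. The same allowance would turn 1.46 into 1.57, so it does not rescue the pair.

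Finally, 1.79 is one approximation, and methods that use the event split give 1.62 to 1.65 for a harmful factor. That is a reason to name the formula; those values do not support 2.00.

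**Conclusion.** The concern holds. Under the stated inputs (220 events, two-sided 5%, 80% power, Cox model) the detectable relative risk at 12% prevalence is about 1.79 by the formula that reproduces 1.46. The stated 2.00 has about 92% power by that formula and about 97% in simulation. The discrepancy is conservative. It rests on reading 22% as the whole-cohort incidence and on the Schoenfeld formula, but none of the other readings and methods tried recovers both figures. The article does not show whether the relative risk, the prevalence or an undisclosed event count is the source; one published planning figure is wrong in any case.

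**What to change.** The authors should go back to their calculation, name the formula, and restate the second figure in one of these ways:
- 12% prevalence with a relative risk of 1.79 or higher, if the relative risk is the slip;
- 8% prevalence with a relative risk of 2.00 or higher, if the prevalence is the slip;
- if 2.00 came from a reduced event count (attrition or covariate adjustment), state the reduction and apply it to both cases, giving about 1.57 at 50% and 2.00 at 12%.

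The cost is one sentence. Cohort size, endpoints, analyses and conduct are unchanged.
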